### Eligibility Criteria

Inclusion criteria are as follows: enrolled in one of the classes randomly selected in the 2 middle schools designated, affiliated with or benefiting from a social security system, who will agree to participate in the study and whose parents or holders of parental authority will sign a free, informed, and written consent. Exclusion criteria (intervention group only) are as follows: hypersensitivity to the active substances or to one of the excipients of the vaccine (Gardasil 9), a permanent contraindication to vaccination, pregnant or breastfeeding (based on self-reporting), already initiated HPV vaccination (complete or incomplete schedule), or eligible to participate for collection of data but not for vaccination in the health bus; students with an incomplete vaccination schedule will be referred to their general practitioner to complete the missing doses. Vaccinations will be performed by a junior doctor under the supervision of a senior doctor.

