##### June: Data Collection in Randomly Selected Classes

At the end of school year (June), an investigator will collect data from health records at a specific time during class. In particular, the researcher will look for the presence of de novo HPV vaccination performed by general practitioners outside of the health bus. Signed consent of parents or holders of parental authority will be collected before any intervention in the study (ie, before data collection and before school vaccination is carried out).

Vaccination data, even if not collected at the time of the intervention, can be collected either during the vaccination campaigns, or during the intervention at the end of school year, especially for children whose parents have agreed to participate but not to be vaccinated in the health bus. Indeed, since vaccination dates appear in the health record, it will be possible afterward to know whether pupils were vaccinated before the interventions under study in order to have the vaccination rate at the very beginning of the study.

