### Statistical Analyses

#### Sample Size

To our knowledge, there are no recent studies that have evaluated the impact of school-based vaccination on HPV vaccination coverage rates. An experimental catch-up vaccination program (diphtheria, tetanus, poliomyelitis, pertussis, measles, mumps, rubella, meningococcus C, hepatitis B, and HPV) in schools in the Vosges (Eastern France) [18] showed a participation rate ranging from 42.9% in the first year to 29% in the second year.

The calculation of the study size is based on the expected proportion of vaccination among girls, as this is the main objective of this study and we have no data for vaccination among boys at this time. Statistical assumptions were as follow:

Proportion of schoolgirls who have had a complete HPV vaccination schedule at the end of school year of 6% in the control group for all students (compared to the 8.1% expected at age 16 years [12])Proportion of schoolgirls with a complete HPV vaccination schedule at the end of the school year of 20% in the intervention group

Thus, 87 girls in each group would need to be included to demonstrate this 14% difference at *α*=.05 and power (1−β=0.80). Assuming 15% nonanalyzable data (lost to follow-up, nonresponse), a total of 103 female students per group would need to be included. As there are roughly as many girls as boys in each class, we would need to include 206 students per group. In order to have an equal representation of each age group, the sampling will be stratified in the grades: 6th, 7th, 8th, and 9th grade. Thus, 52 students per grade and per group should be included.

If we consider that the classes contain an average of 22 students each, a minimum of 3 classes per grade should be randomly selected in each of the 2 middle schools to ensure the minimum necessary recruitment. Thus, randomly selecting 3 classes per grade in each of the 2 middle schools will make it possible to include approximately 132 female students per group and thus to ensure the minimum necessary recruitment. A total of 528 students are expected to be recruited (264 girls [132 per group] and 264 boys [132 per group]). The calculation of the number of subjects required was performed with PASS (version 15, NCSS) software.

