The analysis of barriers to vaccination will describe the causes of nonvaccination reported for students who did not initiate the vaccination schedule. Analyses will be performed for girls and boys separately. We will also compare sociodemographic data, medical history, and health care utilization data between students who initiated HPV vaccination at the end of the school year and those who did not in the intervention group. Bivariate comparisons of percentages will be performed by the chi-square test or Fisher exact test depending on validity conditions. For continuous variables, comparisons will be made using the Student *t* test or the Mann-Whitney *U* test, depending on the conditions of validity. A multivariate analysis by logistic regression will be carried out in order to take into account confounding phenomena: the variable to be explained will be the fact of having initiated vaccination at the end of the school year, and the explanatory variables entered in the model will be the variables for which the significance threshold in bivariate analysis will be ≤.20.

To be determined in the intervention group: among students who initiated HPV vaccination at the end of school year, the proportion of students who used the health bus to initiate this vaccination. Among students who completed the full vaccination schedule at the end of school year, we will determine the proportion who completed all injections on the health bus.

In the intervention group, the proportion of students who used the health bus for sexual health information will be evaluated. In the intervention group, positive and negative points reported by students, their parents, and school staff about this program will be described. Proportion of students up to date for each type of vaccine (according to current vaccination calendar) at the end of school year, in the entire study population as well as in each of the 2 groups (intervention and control), and comparison of these proportions between the 2 groups by the chi-square test or Fisher exact test will be determined, according to validity conditions.

Analyses comparing control group to intervention group will all be performed on an intention-to-treat basis. All hypotheses will be tested with bilateral tests and *α*=.05 and confidence interval calculated at 95%. Analyses will be performed using SAS (version 9.4, SAS Institute Inc) software.

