### Strengths and Limitations

This protocol is submitted more than a year after recruitment began, since sanitary COVID-19 condition was in constant change and evolution and it was difficult to know whether we could continue the process of the trial. Amendments were made and submitted to the ethics committee, facing prohibition of meetings with more than 6 people. This protocol is the result of our constant adaptation to these different obstacles.

Having different exclusion criteria for participants in the intervention and control arms m ay introduce a selection bias by design. However, we wanted to include as many children as possible in the control group to have a representative sample of the population, and the groups may still be comparable. The sample size calculation has not taken into account correlation between participants in the same cluster. As such, the sample size is likely to be too small. However, one limit is the price of the vaccine, which limited our ability to include more students, with regard to the funds allocated.

On Reunion Island, specificities regarding economic and societal development are as follows: high rate of universal health insurance coverage where the high cost of HPV vaccine may be a barrier, mixed culture with religious faith incompatible with premarital sex and racist biopolitical mistrust of the West from which the vaccine comes from, and the particular weight of the antivaccine leagues which casted a negative halo around the subject [25]. Thus we expect a strong veto from parents.

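### Prior HPV vaccination is listed as an exclusion in the intervention group only, in a clause that can also be read as keeping those girls in; the rule for the primary analysis must be stated once, for both schools

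*Protocol article*

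**What the plan says.** All of the following is in the protocol article.

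- **Eligibility Criteria.** The list opens with "Exclusion criteria (intervention group only) are as follows". It covers hypersensitivity, permanent contraindication, pregnancy or breastfeeding, and then pupils who "already initiated HPV vaccination (complete or incomplete schedule), or eligible to participate for collection of data but not for vaccination in the health bus". Pupils with an incomplete schedule are referred to their general practitioner. No matching rule is given for the control school.
- **Objectives; Statistical Methods for Primary and Secondary Outcomes.** The primary outcome is the proportion of girls with a full schedule by the end of the school year, compared between schools by chi-square or Fisher exact test. It has no start date and is not limited to doses given during the study. Comparability at inclusion is to be checked, and between-group analyses are by intention to treat.
- **Sample Size.** The assumptions are "complete HPV vaccination schedule at the end of school year of 6% in the control group for all students", set beside 8.1% at age 16, and "complete HPV vaccination schedule at the end of the school year of 20% in the intervention group". They give 87 girls per group, 103 after a 15% allowance, with about 132 per group expected.
- **June data collection.** Because dose dates are in the health record, "it will be possible afterward to know whether pupils were vaccinated before the interventions under study", so that a starting vaccination rate can be obtained.
- **Strengths and Limitations.** "Having different exclusion criteria for participants in the intervention and control arms" is acknowledged as a possible source of selection bias. No direction, size or remedy is given.

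**The concern.** The characteristic excluded in one arm is closely tied to the outcome. A girl who completed her schedule before the program is, by definition, a success at the end of the year. If she is dropped from the intervention school and kept in the control school, the intervention proportion is new completion among never-vaccinated girls and the control proportion is total coverage among all girls. The intention-to-treat statement does not repair this, because the populations already differ at entry.

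The clause does not settle whether this happens. A pupil eligible for data collection cannot sensibly also be excluded from the study, yet both descriptions stand in one list of exclusions. Two analysts could build different primary denominators from the same text.

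**Working it through.** **1. Inputs.** From Sample Size: 6% control, 20% intervention, α = 0.05, power 0.80, 87 per group, 15% non-analysable, about 132 girls expected per group. From Statistical Methods: two-sided testing ("All hypotheses will be tested with bilateral tests"). Assumed, because the documents do not give it: a share b of girls in each school who had completed before the program, taken as 0% to 6%. The value 6% is an upper bound, because it uses up the whole end-of-year control rate and leaves no new completions in the control school.

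**2. The plan's own figure.** Normal approximation with unpooled variance:

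(1.960 + 0.842)² × (0.06 × 0.94 + 0.20 × 0.80) / 0.14² = 86.7, rounded up to 87.

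87 / 0.85 = 102.4, rounded up to 103. Both stated figures reproduce. Exact binomial power of the uncorrected chi-square test at 87 per group is 81%.

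**3. Exclusion applied in the intervention arm only.** Take 20% and 6% as cumulative coverage among all girls. Removing the share b from the intervention numerator and denominator gives an observed rate of (0.20 − b)/(1 − b), while control stays at 6%. Power is for the same exact test, with n control girls and n(1 − b) intervention girls. It is shown at n = 87 and at n = 112, the analysable number if 132 are recruited and 15% are lost (132 × 0.85 = 112.2).

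| b | Intervention rate | Difference from 6% | Power, n = 87 | Power, n = 112 |
|---|---|---|---|---|
| 0% | 20.0% | 14.0 points | 81% | 90% |
| 2% | (0.20 − 0.02)/0.98 = 18.4% | 12.4 points | 71% | 82% |
| 4% | (0.20 − 0.04)/0.96 = 16.7% | 10.7 points | 62% | 73% |
| 6% | (0.20 − 0.06)/0.94 = 14.9% | 8.9 points | 48% | 58% |

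**4. Direction under no effect.** Suppose true coverage is 6% in both schools. The intervention arm would then show (0.06 − b)/(1 − b), which is 4.1%, 2.1% or 0% for b = 2%, 4% or 6%. At n = 87 the test would favour control with probability 7%, 24% or 77%, against a nominal 2.5% in that direction. So the effect is bias as well as lost power, and it runs against the program.

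**5. One rule in both arms.** Keeping all girls in both schools leaves 20% against 6%, a 14-point difference. Removing prior completers from both gives 18.4% against 4.1% (14.3 points) at b = 2%, and 16.7% against 2.1% (14.6 points) at b = 4%. Either symmetric rule avoids the shrinkage.

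**6. Limits of the illustration.** Girls with an incomplete earlier schedule are on the same list. Removing them from one arm would shift the figures further, and the documents give no number for them. These calculations, like the plan's, treat girls as independent.

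**The case against.** The strongest reply is that the exclusion was never meant to reach the analysis. The other listed criteria are reasons not to vaccinate someone, which suggests that the list governs access to the bus. The same sentence says that some pupils may take part in data collection only. The June section plans a starting vaccination rate from dose dates, and in the intervention school that rate would be zero by construction if already vaccinated pupils had been removed. Vaccination status is recorded at inclusion and at the end. On this reading both arms measure total coverage, as the objective says. This is plausible and cannot be ruled out. It does not close the point, because the text still lists these pupils as excluded, the limitations paragraph says that participants' criteria differ by arm, and nowhere is it said that already vaccinated intervention girls enter the primary analysis.

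A reader might go further and infer that the primary contrast fails to estimate the program's impact on either reading. The documents do not support that. If the girls stay in, the comparison matches the stated objective. A starting difference between schools is then confounding from having one non-randomised school per arm, and does not come from the eligibility rule. The planned check of comparability at inclusion addresses it in part, although the primary test does not adjust for it.

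Three points about size also stand. The share b is assumed. The 20% may have been meant for eligible girls only, in which case the calculated loss disappears. At the expected recruitment and b = 2%, power stays above 80%. Finally, the authors disclose the differing criteria, but disclosure without a remedy leaves the analysis rule open.

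**Conclusion.** The point holds as an unresolved contradiction with a real consequence on one reading. It does not show that the two arms certainly measure different things.

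- **If the exclusion is applied to the analysis as listed,** the contrast is biased against the program. With 20% and 6% taken as coverage among all girls, the 14-point difference shrinks to 12.4, 10.7 or 8.9 points for b = 2%, 4% or 6%. Power is 71%, 62% or 48% at 87 per group (82%, 73% or 58% at about 112), against 81% (90%) without the exclusion. The last value in each set is the worst case.
- **If the girls stay in,** the definition is common to both arms. The remaining weakness is that the primary test takes no account of a starting difference between two designated schools.

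The direction on the first reading is firm. Its size rests on an assumed b and on what the 20% was meant to describe.

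**What to change.** Vaccination recruitment was complete by June 2021 and analyses were still under way at publication, so the change is to the wording and to the analysis set.

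1. Reconcile the clause in Eligibility Criteria. State separately who could be vaccinated on the bus and who is analysed, so that prior vaccination does not decide membership of the analysis set.
2. State one primary rule for both schools: all consenting girls (intervention) or non-objecting girls (control), whatever their prior vaccination. This fits the stated objective and the 6% and 20% assumptions.
3. Add supporting analyses from the dose dates: (a) girls with no HPV dose before a common start date, in both schools; (b) coverage at the start and end in each school, with the difference in change.
4. If the unvaccinated-only set is made primary instead, restate the 6% and 20%, which then describe a different population.

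The cost is a little extra analysis. If the records of already vaccinated intervention girls were not collected, only the analysis of girls unvaccinated at the start in both arms is available, with a few percent fewer girls; the report should say so.

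### Conditions for not being vaccinated on the health bus are printed as study exclusions for the intervention school only, in conflict with the June data collection and the intention-to-treat statement

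*Protocol article*

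**What the plan says.** Protocol article, Eligibility Criteria, opens the list with "Exclusion criteria (intervention group only) are as follows". The items are hypersensitivity to the vaccine, a permanent contraindication, pregnancy or breastfeeding, HPV vaccination already started or complete, and finally "or eligible to participate for collection of data but not for vaccination in the health bus". The text then adds that "students with an incomplete vaccination schedule will be referred to their general practitioner to complete the missing doses". No exclusions are given for the control school.

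The section on June data collection, which is part of the intervention group's description, says that vaccination data can also be gathered at the end of the year, "especially for children whose parents have agreed to participate but not to be vaccinated in the health bus". In the same visit the investigators look for doses given by general practitioners outside the bus.

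Statistical Methods for Primary and Secondary Outcomes states: "Analyses comparing control group to intervention group will all be performed on an intention-to-treat basis". The primary outcome is the proportion of schoolgirls with a full regimen at the end of the school year, compared by chi-square or Fisher exact test.

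Strengths and Limitations acknowledges that the arms have different exclusion criteria and that this may cause selection bias. The reason given is that "we wanted to include as many children as possible in the control group".

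**The concern.** The intervention is a whole program: information, training of general practitioners, and the bus. A girl in the intervention school who cannot or may not be injected on the bus has still been exposed to it, and her status at the end of the year is part of the program's result. Excluding her turns a condition for giving an injection into a condition for being counted.

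The control school has no matching rule, so a comparable girl there stays in, most likely as a non-completer. The primary comparison would then rest on two differently defined denominators, and the difference in proportions would partly reflect who was counted. The article admits the asymmetry but gives neither its direction nor its size, and sets no remedy.

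**Working it through.** **1. The texts side by side.**
- Eligibility Criteria: data-only pupils appear as the last item of an exclusion list, yet the item itself calls them eligible to take part.
- June data collection: children whose parents agreed to participate but not to bus vaccination have their records read.
- Statistical Methods: all between-group comparisons are by intention to treat.

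A girl cannot be excluded under the first and counted under the other two. No section says whether she is in the primary denominator.

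**2. The plan's own figures.** Sample Size gives 6% in control, 20% in intervention, two-sided α = 0.05 and power 0.80. With the unpooled formula:

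n = (1.960 + 0.842)² × (0.06×0.94 + 0.20×0.80) / 0.14² = 86.7, so 87 per group.

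With 15% non-analyzable, 87/0.85 = 102.4, so 103. Both stated figures reproduce and are not in dispute. They supply the base rates below.

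**3. One-arm removal of girls who do not complete.** Let e be the share of intervention girls removed, none of whom completes. The observed proportion is 0.20/(1 − e).

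| e (assumed) | Observed for a true 20% |
|---|---|
| 2% (medical reasons only) | 20.4% |
| 5% (medical reasons only) | 21.1% |
| 10% | 22.2% |
| 20% | 25.0% |
| 30% | 28.6% |

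The documents give no value for e. The 5% equals the adolescent pregnancy rate in Future Directions, used here only as a high value for the medical items. If the removed girls complete at rate q, the observed value is (0.20 − e·q)/(1 − e). At e = 30% this is 28.6% for q = 0, 26.0% for q = 6%, and 20.0% for q = 20%. The table is therefore an upper case.

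**4. Adding the other one-arm exclusion.** Let b be the share of intervention girls removed because they are already complete. The observed proportion is (0.20 − b)/(1 − b − e).

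| | e = 10% | e = 20% | e = 30% |
|---|---|---|---|
| b = 2% | 20.5% | 23.1% | 26.5% |
| b = 4% | 18.6% | 21.1% | 24.2% |
| b = 6% | 16.7% | 18.9% | 21.9% |

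Setting the expression equal to 0.20 gives e = 4b. The two effects cancel at e = 8%, 16% and 24% for b = 2%, 4% and 6%. Below that line the intervention rate is understated; above it, overstated. The documents do not give b either.

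**5. Effect on the test if the program does nothing (6% in both schools).** This uses full binomial enumeration of the two-sided 0.05 chi-square test, with 103 control girls, 103 × (1 − b − e) intervention girls, and intervention rate (0.06 − b)/(1 − b − e).
- Nothing removed: falsely favours the program with probability 0.024.
- e = 30%, b = 0: 0.098.
- e = 30%, b = 2%: 0.028.
- e = 30%, b = 4%: 0.002.
- e = 2% to 5%, b = 4%: falsely favours the control with probability about 0.26 to 0.28.

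**The case against.** The strongest reply is that removal from the denominator is inferred. The disputed clause follows the item on pupils who have already started vaccination and precedes the sentence sending partly vaccinated pupils to their general practitioner. It may be a garbled remark about those pupils, meaning that they give data but are not injected on the bus. The June collection, the intention-to-treat statement and the planned analyses of non-vaccination and of bus use all suggest that such pupils are kept. Analysis-set detail may also sit in the full protocol or the analysis plan, neither of which is shown. All of this stands as doubt about what the investigators meant. It does not settle the printed text: the medical items are still intervention-only exclusions, and Strengths and Limitations confirms that the arms differ.

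A reader might go further and infer that the list biases the primary result in favour of the program, perhaps severely. The documents do not support that, for three reasons.
- Large removed shares have no source. The article expects strong parental opposition but gives no proportion, and parental refusal is not itself on the exclusion list.
- Girls not vaccinated on the bus can complete with a general practitioner, a route the program promotes and the June visit looks for.
- The exclusion of girls already vaccinated acts in the opposite direction and can cancel or outweigh the effect (steps 4 and 5).

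A reader might also infer that an enrolled girl who becomes pregnant during the year would be dropped from analysis. No section says so; the check before each injection governs only the injection.

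**Conclusion.** The point holds as a contradiction about who is counted. Conditions for not injecting on the bus are written as study exclusions in one school only. The data-only item contradicts itself, the June data collection and the intention-to-treat statement, and acknowledging possible selection bias does not resolve this.

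Taken alone and read literally, the rule raises the intervention proportion. The rise is small for the medical items (20% becomes 20.4% to 21.1%) and larger only if data-only girls are also removed in number (22.2% to 28.6% for 10% to 30%). These values assume the shares removed and assume that none of those girls completes, so they are bounds for illustration and not expected effects. With the exclusion of already vaccinated girls included, the net bias can go either way. Neither its sign nor its size can be fixed from the documents.

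**What to change.** Reconcile Eligibility Criteria with the June data collection section and the intention-to-treat statement.
- Relabel the intervention-only list as criteria for not being vaccinated on the health bus, and state that meeting one of them does not exclude a pupil from the study. This leaves the conditions for giving the injection as they are.
- Remove the data-only clause as an exclusion. If it was meant to describe pupils who have already started vaccination, say so.
- Set one primary denominator rule for both schools: every girl in the drawn classes whose data may be collected is counted by her recorded vaccination status at the end of the school year, whether doses were given on the bus or elsewhere.

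The cost is wording and an analysis-set definition. The reported intervention coverage may change slightly. The article says analyses were still ongoing, so the rule should be fixed before the primary result is produced.
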